### Study visits and procedures

#### Screening

Interested individuals will be reviewed by the study doctor at a screening visit (34+0 to 36+6 weeks gestation), to discuss the study timeline and procedures (table 2) and assess eligibility (box 1). Eligible individuals who provide informed consent at screening will be considered enrolled. A detailed medical history will be taken, followed by pharyngeal and saliva sampling to assess for *N. lactamica* carriage; enrolled volunteers who are already naturally colonised with *N. lactamica* will not be inoculated. However, they will be invited to remain in the study as an opportunistic comparison cohort, and will complete all postpartum visits and sampling as for the inoculated mother–neonate pairs (table 2).

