*Neisseria lactamica* nasal inoculation		+ (Unless already colonised)				
Nasopharyngeal swabs (mother)	+	+	+	+	+	+
Oropharyngeal swabs (mother)	+	+	+	+	+	+
Saliva swabs (mother)	+	+	+	+	+	+
Nasopharyngeal swabs (infant)			+	+	+	+
Saliva swabs (infant)			+	+	+	+
Umbilical cord blood			Optional			
Infant venous blood (2 mL)					Optional	Optional
Maternal breast milk			Optional	Optional	Optional	Optional
Maternal venous blood (5 mL)						Optional
Oropharyngeal and saliva swabs (under 5 years)						Optional

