### *N. lactamica* sequencing

If any neonates become colonised with *N. lactamica*, paired mother–infant *N. lactamica* isolates will undergo whole genome sequencing to assess for differences in *N. lactamica* microevolution in mother–infant pairs. Resulting sequences will be mapped to a closed *N. lactamica* Y92-1009 reference genome for comparison.

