### Sample size

To our knowledge, this proof-of-concept represents the first respiratory controlled human infection study in pregnancy. As such, it is not possible to accurately define the sample size needed to conclusively rule out induced horizontal transfer of *N. lactamica*. A pragmatic sample size of 20 inoculated volunteers has been selected: based on our earlier work, *N. lactamica* colonisation is expected in 18 (90%) of volunteers inoculated with 10^5^ CFU *N*. *lactamica*. This sample would therefore fail to detect horizontal transfer only if it occurs in less than 1 in 18 infants (<6%), in which case it would be impractical and even unethical to pursue horizontal *N. lactamica* controlled human infection as a method of studying and manipulating infant commensalisation. By 1 month of age, 2.3% of infants naturally carry *N. lactamica*.^17^ Based on a plot of lower confidence limits against observed infant *N. lactamica* colonisation for a sample of 18 experimentally-colonised volunteers, infant *N. lactamica* colonisation greater than 22% (95% CI (2.3% to 41.7%)) would demonstrate that inoculation-induced carriage exceeds natural *N. lactamica* carriage (figure 2).

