**Figure 2 F2:**
[figure not shown]
Lower confidence limit plot for inoculation-induced *Neisseria lactamica* (Nlac) colonisation.

We expect to screen at least 24 volunteers to reach our target of 20 inoculations, allowing for 10% dropout and 10% baseline natural *N. lactamica* carriage.^18^ It is not clear how maternal or neonatal antibiotics may influence *N. lactamica* carriage and microbiota. At the Principal Investigator’s discretion, an additional volunteer may be enrolled and inoculated for every volunteer (or neonate) who receives antibiotics after inoculation, up to a maximum of 10 additional volunteers.

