### Statistical analysis

The primary endpoint will be expressed as a proportion N/M, where:

M=Number of mothers colonised with *N. lactamica*.N=Number of neonates (aged 0–31 days) colonised with the same strain of *N. lactamica* as their own mother.‘Colonised’=evidence of *N. lactamica* by culture of upper respiratory swabs (using selective media and confirmation by API or MALDI-TOF) on at least one visit.‘Same strain’=confirmed using Y92-specific *N. lactamica* PCR for inoculated volunteers, or whole genome sequencing for volunteers already naturally carrying *N. lactamica* at screening.

Subgroup analysis will be performed, to compare inoculated mother–infant pairs with naturally colonised mother–infant pairs, and to compare pairs where the mother or infant received antibiotics with pairs not receiving antibiotics.

Specific bioinformatic analysis strategies will depend on the quantity and quality of genomic data produced during the study, and on the rates of *N. lactamica* colonisation observed. Broadly speaking, microbiome bioinformatic pipelines (eg, QIIME2 and R packages) will be used to perform taxonomic classification, calculation of alpha and beta diversity and data visualisation.

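### The inoculated-versus-natural comparison counts mothers who lose carriage before birth in one denominator but not the other, and rests on about 2 natural pairs

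*Protocol article*

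**What the plan says.** The Statistical analysis section of the protocol article expresses the primary endpoint as N/M. M is the number of mothers colonised, and N is the number of neonates aged 0–31 days who carry their own mother's strain. Colonised means at least one culture-positive visit, with no restriction to visits after inoculation or after birth. The section then adds: "Subgroup analysis will be performed, to compare inoculated mother–infant pairs with naturally colonised mother–infant pairs".

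The natural group comes from screening at 34+0 to 36+6 weeks. Volunteers already carrying *N. lactamica* are not inoculated; instead "they will be invited to remain in the study as an opportunistic comparison cohort" and follow the same postpartum visits. Under the Inoculation section, only volunteers not already naturally colonised are inoculated, at 36+0 to 37+6 weeks. In Table 2 the maternal swabs fall at screening, at the inoculation visit, at birth and at the later visits.

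Strain match is judged by a Y92-specific PCR for inoculated volunteers and by "whole genome sequencing for volunteers already naturally carrying" the organism at screening. Separately, if any neonate is colonised, the paired mother–infant "isolates will undergo whole genome sequencing to assess for differences".

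On size, the Sample size section says: "A pragmatic sample size of 20 inoculated volunteers has been selected". It adds that "colonisation is expected in 18 (90%) of volunteers inoculated with" the planned dose, and "We expect to screen at least 24 volunteers to reach our target of 20 inoculations", allowing for 10% dropout and 10% natural carriage. Up to 10 more volunteers may be added where antibiotics are given.

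**The concern.** M is worded identically for both groups, but the visit schedule makes it select different mothers. A woman who loses carriage before delivery stays in the natural denominator, through her screening swab. The same woman in the inoculated group is never recorded as experimentally colonised and drops out of M. An infant is exposed to its mother's pharyngeal flora from birth. The natural N/M would therefore include mothers with nothing to pass on, while the inoculated N/M would mostly exclude them. A gap between the two proportions could then come from the entry rule rather than from any difference in transmission.

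The plan's own figures also imply a very small natural group. A reader who sees two proportions set against each other could take either a gap or its absence as evidence on how experimental carriage compares with natural carriage. The data could support neither reading.

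**Working it through.** **1. The plan's own figures.**
- Colonisation after inoculation (the *N. lactamica* inoculum section): 100% of 10 and 85% of 20 adults, so (10 + 17)/30 = 90%, and 0.90 × 20 = 18. Reproduced.
- Number screened: 20 × (1 + 0.10 + 0.10) = 24. Reproduced. Dividing instead, 20/(0.9 × 0.9) = 24.7, gives 25, which changes nothing here.

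**2. Who enters M.**

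| Mother's course | Natural carrier | Inoculated |
|---|---|---|
| Culture-positive at birth or later | In M | In M |
| Carriage lost before birth and not regained | In M (screening swab) | Experimental carriage never recorded; not in M |

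The groups differ only in the second row.

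**3. Possible size of the effect (illustration).** Let *t* be transmission from mothers carrying at birth, equal in both groups. Let *s* be the share of screening carriers still positive at birth. Assume no transmission from mothers who cleared earlier, and that every inoculated mother in M carries at birth. Then inoculated N/M = *t* and natural N/M = *t* × *s*. With *t* = 22% (the plan's threshold for infant colonisation):
- *s* = 0.5: 11% against 22%
- *s* = 0.7: 15% against 22%
- *s* = 0.9: 20% against 22%

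The values of *s* are assumptions; the article gives none.

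**4. Size of the natural group.**
- Expected: 24 × 0.10 = 2.4, or 2.4 × 0.9 = 2.2 after dropout.
- Binomial(24, 0.10): P(none) = 0.9^24 = 8%; P(2 or fewer) = 56%; 95% range 0 to 6.
- With all 10 additional volunteers, 30 are inoculated. Screening is then 30 × 1.2 = 36 to 30/0.8 = 37.5, rounded up to 38. That gives 3.6 to 3.8 natural carriers, or 3.2 to 3.4 after dropout.

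**5. Precision.** The exact (Clopper–Pearson) upper limit for 0/2 is 1 − 0.025^(1/2) = 84%, and the lower limit for 2/2 is 0.025^(1/2) = 16%.
- 0/2: 0–84%
- 1/2: 1–99%
- 2/2: 16–100%
- With 4 pairs: 0–60% for 0/4 and 40–100% for 4/4

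**6. If a test were applied.** The article names none; a two-sided Fisher test at 0.05 is assumed.
- 4/18 against 2/2: C(6,2)/C(20,2) = 15/190 = 0.079
- 3/18 against 2/2: C(5,2)/C(20,2) = 10/190 = 0.053
- 4/18 against 3/3: C(7,3)/C(21,3) = 35/1330 = 0.026

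With exactly 2 natural pairs, no inoculated result from 3/18 to 15/18 can reach p < 0.05. With 3 pairs it can, at the extreme. Exact power against an inoculated rate of 22%:
- 18 against 2 pairs: 5% if the natural rate is 50%, 12% if it is 75%
- 27 (= 0.9 × 30) against 3 or 4 pairs: 13–18% and 39–50% respectively

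**The case against.** The strongest reply is that the article calls this cohort opportunistic, states no test, error rate or equivalence claim, and hangs no decision on it. The sample size argument sets infant colonisation against 2.3% natural infant carriage, not against this group. How a subgroup is presented is normally left to an analysis plan, which is not shown. All of that stands and keeps the point modest. It does not answer the entry rule, which the article itself fixes and which a larger natural group would not cure.

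Two further objections stand in part. First, the net direction of bias is not proven. M counts any strain, so an inoculated mother who carries and passes on a wild strain is in M but not in N, which pulls the other way. An inoculated mother may also enter M on a visit after birth. Second, with about 2 natural pairs the entry effect would be hidden within the interval, so a reader would not see it as a measurable distortion.

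A reader might infer that the two strain-match methods bias the comparison. The article does not support this. A Y92-specific PCR cannot establish identity between natural strains, so another method is needed for that group. The strain-specific PCR section reports that the Y92 band pattern has not been reproduced in circulating strains, and no misclassification is shown.

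**Conclusion.** The point holds as one about this comparison only. The two denominators are not alike, because carriage before birth counts for natural carriers but experimental carriage before birth cannot be recorded in inoculated mothers. The entry rule on its own lowers the natural N/M. The amount depends on persistence and transmission values that the article does not give; the figures of 11–20% against 22% are illustrative.

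The comparison can support almost no inference at about 2 natural pairs. That number assumes 24 screened, 10% carriage, 10% dropout and that all carriers accept the invitation to stay.

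It would go too far to say that a non-significant result is guaranteed or that the comparison is worthless. The figure of 2 is an expectation, 3 or more carriers among 24 has probability 1 − 0.56 = 44%, and an extreme result with 3 pairs would reach significance under the assumed test. Nor does the article claim equivalence or plan to test for it.

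**What to change.** For this comparison only:

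1. Define M in both groups as mothers culture-positive at one or more of visits 3 to 5. Visit 5 ends at 28 + 3 = 31 days, so this window matches the neonatal window of 0–31 days used for N. It also keeps the optional 15-week visit out of M.
2. Report the two sets of counts side by side with exact 95% confidence intervals, as description, without a test and without a claim of difference or similarity.
3. As a secondary check, confirm the PCR strain match in inoculated pairs against the whole genome sequencing of paired isolates already planned in the *N. lactamica* sequencing section.

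This needs wording only: no new visits, samples or sequencing, and no change to the primary proportion. The cost is that natural carriers who cleared before birth and stay negative leave this comparison. On the persistence values assumed above, the expected 2.2 pairs would become 2.2 × 0.5 = 1.1 to 2.2 × 0.9 = 2.0. Those mothers can still be listed separately.

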### Patient and public involvement

During early study design, an interview-based patient and public involvement project was conducted with 12 pregnant women (unpublished data). All 12 women expressed approval that the proposed study should go ahead, 11 of whom would personally have liked to participate. These discussions led to changes in study design (such as offering follow-up visits in the volunteer’s own home, and obtaining an umbilical cord rather than an infant venous blood sample at birth). During participant recruitment following study completion, the University of Southampton Public Engagement Research Unit will assist in showcasing the study at public engagement events.

## Ethics and dissemination

### Ethics and safety

Volunteer safety and ethical study conduct is of paramount importance. This study has been approved by the NHS Research Ethics committee and the Health Research Authority, and is sponsored by the University of Southampton. An External Safety Committee has been appointed to provide independent safety oversight. Safety of *N. lactamica* Y92-1009 inoculum is well-characterised: over 400 adults have previously been inoculated with this *N. lactamica* strain (of whom 30 received lyophilised inoculum, and 54 received 10^5^ CFU), with no serious adverse reactions reported to date^15^ (unpublished data). Due to the use of yeast-based and soya-based products in inoculum production, individuals reporting allergies to yeast or soya will not be eligible for enrolment. Inoculation will take place in a clinical area with access to adult, obstetric and paediatric emergency services. Volunteers will be reviewed by a study doctor immediately prior to and 30 min after inoculation.

Adverse events will be recorded throughout the study, and volunteers will be encouraged to report any concerns (including by telephone to the study doctor out-of-hours). Adverse events will also be recorded for any inoculated withdrawn volunteers, by telephone review at 4 weeks post partum. As per the current Good Clinical Practice guideline,^25^ adverse events are any untoward medical occurrence in a volunteer or their neonate, temporally, but not necessarily causally, related to study participation. Delivery of routine peripartum care is not considered an adverse event. Serious adverse events include hospitalisation (or prolongation of hospitalisation for routine peripartum care), persistent or significant disability, a life-threatening occurrence or death from any cause.

Mitigation strategies are in place to minimise the risk of SARS-CoV2 transmission to participants and study staff. Where possible, study visits will be conducted in the volunteer’s home, practicing social distancing and appropriate personal protective equipment for non-aerosol generating procedures. If participants report symptoms of or contact with anyone with suspected or confirmed SARS-CoV2 infection, study visits will be rescheduled until testing or self-isolation as necessary.

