## Methods and analysis

### Study overview

In this prospective controlled human infection study, 20 healthy pregnant women will receive nasal inoculation with 10^5^ CFU *N*. *lactamica* (wild type strain Y92-1009) at 36+0 to 37+6 weeks gestation (figure 1). Upper respiratory samples and breastmilk will be collected from mother–infant pairs 1 day, 1 week and 1 month post partum, as well as an umbilical cord blood sample at delivery and an infant venous blood sample at 1 month post partum. Adverse events and relevant clinical data (including mode of delivery, infant feeding and use of antimicrobials) will be recorded. Samples will be analysed by microbiological culture, targeted PCR and sequencing to determine *N. lactamica* Y92-1009 presence, colonisation density and longitudinal microevolution, as well as 16S rRNA gene sequencing to characterise microbiome evolution in mother–neonate pairs.

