### Study hypothesis, objective and endpoints

We hypothesise that nasal inoculation of pregnant women with 10^5^ CFU *N*. *lactamica* strain Y92-1009 will result in maternal upper respiratory *N. lactamica* colonisation; and that horizontal transmission of upper respiratory *N. lactamica* will occur from experimentally-colonised women to their infants by 4 weeks post partum.

This study aims to investigate this hypothesis, and to characterise the safety, colonisation kinetics and microbiome impact of nasal *N. lactamica* inoculation in pregnancy on mother–neonate pairs (table 1).

**Table 1 T1:** Primary, secondary and safety study endpoints

Primary endpoint Confirmation of neonatal (0–31 days) *Neisseria lactamica* colonisation by selective culture of nasopharyngeal and saliva samples.	Secondary endpoints Confirmation of neonatal *N. lactamica* Y92-1009 colonisation by strain-specific PCR. *N*. *lactamica* colonisation density in inoculated volunteers compared with their infants across study time points and sample niche. Microbiome composition across study time points and sample niche in inoculated volunteers compared with their infants, and in colonised compared with uncolonised infants. *N*. *lactamica* genome sequence for isolates derived from inoculated volunteers compared with their infants across study time points and sample niche.
		Safety endpoints Percentage of inoculated volunteers with adverse reactions or serious adverse events within the study period. Percentage of neonates with serious adverse events within the study period.

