Box 1Inclusion and exclusion criteriaInclusion criteria (all must apply)Healthy adult aged 18 years or over on the day of enrolment.Singleton pregnancy, 34+0 to 36+6 weeks gestation on the day of enrolment.Documentation of a 20-week ultrasound scan with no life-limiting congenital anomalies, and no maxillofacial, otorhinolaryngological or neuroanatomical anomalies.Able and willing (in the Investigator’s opinion) to comply with all study requirements.Able and willing to give written informed consent to participate in the study.Booked to receive antenatal care at University Hospital Southampton NHS Foundation Trust (including any associated community antenatal care facilities), UK.Exclusion criteria (none must apply)Any confirmed or suspected immunosuppressive or immunocompromised state, including: HIV infection; asplenia; recurrent severe infections; or use of immunosuppressant medication (for more than 14 days within the past 6 months, excluding topical and inhaled steroids).Planned use of immunosuppressant medication in later pregnancy or post partum.Occupational, household or intimate contact with any immunosuppressed persons.Participation within the last 12 weeks in a clinical trial involving receipt of an investigational product, or planned use of an investigational product during the study period.Prior participation at any time in research studies involving inoculation with *N. lactamica*.Use of oral or intravenous antibiotics within 30 days prior to the inoculation visit.Planned use of oral or intravenous antibiotics at any time during the study period (eg, for planned elective caesarean section or group B streptococcus colonisation).Allergy to soya or yeast.Previous stillbirth or neonatal death.Pre-pregnancy diabetes mellitus.Any other finding that may (in the Investigator’s opinion): increase the risk to the volunteer (or their fetus/infant or close contacts) of participating in the study; affect the volunteer’s ability to participate in the study and complete follow-up; or impair interpretation of study data.

**Table 2 T2:** Study visits and activities

Timeline	Screening (visit 1)	Inoculation (visit 2)	Birth (visit 3)	Follow-up (visits 4 and 5)		Optional (visit 6)
	34+0 to 36+6 weeks gestation	36+0 to 37+6 weeks gestation	0–24 hours post partum	7±3 days post partum	28±3 days post partum	15±2 weeks post partum
Participant Information Sheet and consent form	**+**					
Clinical review	+	+	+	+	+	+

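### The adverse event definition and the offspring safety endpoint leave out the fetus, so a fetal death after inoculation cannot enter the offspring safety percentage

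*Protocol article*

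**What the plan says.** Inoculation takes place "at 36+0 to 37+6 weeks gestation" (Study overview), so exposure of the offspring begins before delivery.

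The section Ethics and safety defines the events to be recorded: "adverse events are any untoward medical occurrence in a volunteer or their neonate", whether or not they are causally related to the study. Its criteria for a serious event cover hospitalisation or its prolongation, and "persistent or significant disability, a life-threatening occurrence or death from any cause".

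Table 1 sets two safety endpoints. The maternal one is "Percentage of inoculated volunteers with adverse reactions or serious adverse events within the study period". The offspring one is "Percentage of neonates with serious adverse events within the study period".

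The article counts a neonate's age from birth. Statistical analysis defines the numerator of the primary endpoint as "Number of neonates (aged 0–31 days) colonised with the same strain" as the mother, and the primary endpoint in Table 1 uses the same 0 to 31 days.

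The eligibility criteria (Box 1) do consider the fetus. One exclusion covers findings that may "increase the risk to the volunteer (or their fetus/infant or close contacts) of participating in the study", and another is "Previous stillbirth or neonatal death".

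**The concern.** Between inoculation and delivery the exposed offspring is a fetus. The article weighs risk to the fetus when it selects women, but its event definition and its endpoints name only the volunteer and the neonate. A fetus that dies in that interval never becomes a neonate, so the pair leaves both the numerator and the denominator of the only offspring safety percentage.

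The study describes itself as the first respiratory controlled human infection study in pregnancy, and it aims to characterise safety in mother–neonate pairs. The earlier safety record that it cites comes from inoculated adults. Offspring safety is therefore new information, and the percentage that reports it should be able to show the gravest outcome of the exposed period.

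**Working it through.** The article states no figure to reproduce here. The check has two parts: follow one fetal death through the definitions, then count it both ways.

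**Through the definitions**

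1. *Is it an adverse event?* Not in a neonate, because neonates are aged from birth. It can be one in the volunteer, but the text does not say so.
2. *Is it serious?* The list of criteria is open-ended and contains death from any cause and hospitalisation, so it could readily qualify. The text does not say whether a fetal death counts as a death or as an event in the mother.
3. *Maternal endpoint.* If it is assigned to the volunteer, it counts as one among all inoculated women. That percentage pools adverse reactions with serious adverse events, so a fetal death cannot be told apart in it.
4. *Offspring endpoint.* It cannot enter, whatever is decided in steps 1 to 3.

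**The count**

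Inputs:
- 20 inoculated women (Sample size), each with a singleton pregnancy (Box 1).
- At most 10 further inoculations where antibiotics are given (Sample size), hence up to 30.
- Assumption: one stillbirth after inoculation and no serious event in any live-born infant. The article gives no stillbirth rate, and none is claimed here.
- Assumption: the neonates in the endpoint are those of inoculated women, with no losses to follow-up.

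Formulas for exact (Clopper–Pearson) two-sided 95% limits:
- For 0/n: lower limit 0, upper limit 1 − 0.025^(1/n).
- For 1/n: lower limit 1 − 0.975^(1/n); upper limit the p that solves (1 − p)^n + n·p·(1 − p)^(n−1) = 0.025.

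Results:

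| Inoculated | Current wording | All inoculated pregnancies |
|---|---|---|
| 20 | 0/19 = 0% (0 to 17.6%) | 1/20 = 5.0% (0.1 to 24.9%) |
| 30 | 0/29 = 0% (0 to 11.9%) | 1/30 = 3.3% (0.1 to 17.2%) |

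For example, 1 − 0.025^(1/19) = 0.176 and 1 − 0.975^(1/20) = 0.0013.

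**Comparison with no stillbirth at all**

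With 20 live births and no serious event the endpoint reads 0/20 = 0%, upper limit 1 − 0.025^(1/20) = 16.8%. With one stillbirth it reads 0/19 = 0%, upper limit 17.6%. The percentage is the same and the interval slightly wider, so the endpoint hardly distinguishes the two situations.

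**The case against.** The strongest case on the other side is that a stillbirth is already captured. Losing a pregnancy is an untoward occurrence in the volunteer, no causal link is required, and the maternal endpoint has every inoculated woman in its denominator. In the illustration it can show 1/20 = 5%. An External Safety Committee oversees the study, events are recorded throughout, and inoculated women who withdraw are telephoned at 4 weeks post partum. No test or decision rule is attached to the neonatal percentage. The article is also a condensed account, and the full protocol may settle how pregnancy outcomes are classified.

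Much of this stands, and it rules out several stronger readings that a reader might infer:

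- *That a stillbirth would go unrecorded.* The documents do not support this. Recording it as a maternal event is the likely course.
- *That the serious event criteria reach only the volunteer's or neonate's own hospitalisation or death.* The text sets no such limit, and the list is not exhaustive.
- *That the exemption for routine peripartum care would remove it.* A stillbirth is not routine care.
- *That a stillbirth would make the neonatal figure look better than if none had occurred.* It stays at 0% with a slightly wider interval. It is more favourable only by comparison with a count of all exposed offspring.
- *That Box 1 contradicts the event definition.* Considering fetal risk at screening is compatible with reporting events under mother and neonate. Box 1 shows only that the risk was foreseen.

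These points do not repair the offspring endpoint. The article does not leave the matter open: it states the definition and the endpoint, and both stop at the neonate. Even if the death is assigned to the mother, the offspring percentage loses the pair, and the maternal percentage does not identify the event.

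**Conclusion.** The point holds for the offspring safety percentage and for the wording of the event definition, and no further. As written, a fetal death after inoculation cannot be counted in that percentage. Its place in the maternal one is probable but unstated, and there it is mixed with other reactions and events.

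In the illustration the reported figure is 0% instead of 5% with 20 women, or 0% instead of 3.3% with 30. These sizes rest on one assumed stillbirth and no other serious event in the offspring. The documents give no basis for saying how likely that is. What does not depend on the assumption is the rule itself: the endpoint excludes this outcome by definition. For a study that presents itself as the first of its kind in pregnancy, this is worth correcting before results are reported.

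**What to change.** Make three changes of wording:

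1. In Ethics and safety, let the adverse event definition cover a volunteer, or her fetus or infant from the time of inoculation.
2. In the same section, state that fetal death is a serious adverse event.
3. In Table 1, define the second safety endpoint as the percentage of offspring (fetus or infant) of inoculated volunteers with a serious adverse event from inoculation onwards, with every inoculated pregnancy in the denominator.

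No new visit is needed. The birth visit, or the 4-week telephone review for inoculated women who withdraw, can supply the outcome, and no clinical procedure changes. The small costs are that the reported percentage may be less favourable and that one fetal death may appear under both the maternal and the offspring endpoint. A note to the safety table can say when the same event is counted in both.
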